## Abstract

**Background:**

To date, the clinical modulation for bone metabolism based on the neuro-bone mass regulation theory is still not popular. The stimulation of nerve systems to explore novel treatments for Postmenopausal osteoporosis (PMOP) is urgent and significant. Preliminary research results suggested that changes brain function and structure may play a crucial role in bone metabolism with PMOP. Thus, we set up a clinical trial to investigate the effect of the combination of repetitive transcranial magnetic stimulation (rTMS) and catgut embedding in acupoints (CEA) for PMOP and to elucidate the central mechanism of this neural stimulation in regulating bone metabolism.

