The clinical treatment methods for PMOP mainly include medication and non-medication (7–9). Bisphosphonates are still the first-line medicine for OP, but potential long-term adverse reactions must be considered (10). A survey found that 19% of postmenopausal women diagnosed with OP did not receive anti-OP drug treatment, and 52% of patients refused the physician’s recommendation for drug treatment, mainly due to concerns about the potential side effects (11). Possible adverse reactions and patient resistance severely limit the clinical prevention and treatment of PMOP. Catgut embedding in acupoints (CEA) combines traditional acupuncture with modern medical theory. Guided by the idea of ‘deep and long-lasting insertion to treat chronic and stubborn diseases’, absorbable surgical sutures were creatively embedded deeply into acupoints during CEA to achieve sustained stimulation. Many clinical practices and studies have confirmed that CEA for PMOP has the advantages of good efficacy, safety, and reliability (12). The CEA has apparent advantages in overcoming and solving expensive medical costs, drug toxicity, and side effects, shortening traditional acupuncture treatment time, and improving patient compliance, which is worth further research (13). However, high-quality evidence from large-scale multicenter clinical randomized trials is still needed to support the treatment outcomes.

The nervous system also plays a regulatory role in bone remodeling and maintenance of bone mass. Scholars have found many neurotransmitters and hormones related to bone remodeling in the brain or brain-related organs and proposed mechanisms for crosstalk of the brain and bone (14–16). The theory of brain-bone mass regulation is of great significance for studying bone metabolism mechanisms. The brain regulates bone mass through neural-bone formation, neural-endocrine, and neuropeptide-bone regulation networks (17). Based on the methods of the functional magnetic resonance imaging (fMRI) technique, we speculated that the brain function and structure may play a crucial role in bone metabolism with PMOP. The CEA may exert its therapeutic effect on PMOP through the functional connection of the hypothalamic nuclei with the frontal cortex (18). CEA is a peripheral stimulation that regulates bone metabolism through the bottom-up, peripheral-central-peripheral pathway.

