Repetitive transcranial magnetic stimulation (rTMS) generates a robust and rapidly changing magnetic field that induces current in the target area under the coil, thus activating cortical and subcortical neurons. It regulates neuronal excitability or inhibition, evaluates the corticospinal tract, and enhances brain plasticity (19, 20). This technique has been applied to evaluate the motor system, explore brain function, and investigate the pathophysiology of psychiatric disorders (21, 22). rTMS is currently an essential neuromodulation technique that can be used directly by stimulating the central targets in order to treat neurological diseases and peripheral systemic conditions (23, 24). Based on the neuro-bone mass regulation theory, we propose a central stimulation intervention to regulate bone metabolism by using the neuromodulatory effect of rTMS. We hypothesize that the combination of CEA and rTMS may have a coordinated, synergistic, and reaction-reduced effect, which has significant clinical value in exploring better treatment options for PMOP. The prevention and treatment of PMOP should not rely solely on peripheral interventions but also focus on central involvement. It is essential to integrate central and peripheral regulation for bone remodeling with the participation of the central and peripheral nervous systems.

CEA achieves brain bone mass regulation through the bottom-up peripheral-central way, while rTMS achieves it through the top-down stimulation of the central-peripheral (25). The combination of CEA and rTMS may achieve a bidirectional central-peripheral intervention on bone metabolism (26). Consequently, the study aims to explore the clinical effectiveness and safety of rTMS combined with CEA in treating PMOP from the perspective of central-peripheral regulation. We would like to preliminarily investigate the intrinsic correlation between CEA combined with rTMS, brain bone mass regulation, and clinical signs and elucidate the central mechanism of CEA combined with rTMS in regulating bone metabolism.

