#### The rTMS group

2.9.3

The treatment will be completed by a trained professional therapist using a transcranial magnetic stimulator (YRD CCY-II from Wuhan Eredo). The motor threshold (MT) and dorsolateral frontal lobe (DLPFC) stimulation site are to be determined during the first treatment. The room temperature will be maintained at 16°C–23°C, and the patient will be lying flat on their side on the treatment bed. The motor-evoked potentials (MEPs) are to be recorded in the contralateral hand’s interosseous muscle through the magnetic stimulator’s electromyographic amplifier, with the center of the “8” coil placed on the right temporal cortex of the subject. The stimulation site and the stimulation volume are adjusted until at least 5 out of 10 stimulations evoke MEPs with an amplitude more significant than 50 μV, at which point the magnetic flux is MT, and move 4 cm forward horizontally at the site where the MEPs are elicited, which is the DLPFC. We plan to utilize a positioning cap and a transcranial magnetic stimulator (YRD CCY-II from Wuhan Iredell) to accurately identify and target the specific location during the procedure (31). We intend to choose the right DLPFC point as the stimulation site. The stimulation intensity will be set at 80% of the resting movement threshold, with a frequency of 1 Hz, lasting 30s with an interval of 4 s, and 10 series to be performed continuously on the patient (32, 33). The treatment plan will consist of one session per day, 5 days a week, for 4 weeks (34, 35). Starting from the fifth week, the treatment plan changes to twice a week for eight consecutive weeks (36). In total, this treatment plan will last for 12 weeks and include 36 sessions.

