#### Clinical objective indicators

2.11.2

The secondary outcome measures are (i) Leptin, (ii) Leptin Receptor (iii) Noradrenaline. The leptin, leptin receptor, and norepinephrine levels of peripheral blood must be measured before and after treatment.

Blood samples should be collected on the day of entry and the first day after the end of treatment for the CEA group, the rTMS group, and the CEA combined with rTMS group. Before sampling, all required tubes should be prepared and appropriately labeled with the study protocol number, subject number, study phase, period, and date and time of sampling. The authorized research nurse is responsible for collecting the blood specimens. After collection, the tubes are inverted and mixed. Blood is drawn in the order required by the collection process to prevent cross-contamination between different types of boxes. If a tube is contaminated, it should be replaced immediately with a spare tube and re-labeled. Vital signs are recorded before sampling. Blood is drawn from a venous elbow at 8:00 am in the fasting state. 3 mL of blood is collected in a pre-prepared tube, and after being centrifuged, the serum is collected for testing. 5 mL of blood is contained in a pre-prepared anticoagulation tube (20 μL/mL of peptidase, 20 μL/mL of 10% EDTA-Na2), centrifuged, and plasma collected for testing. Collect 5 mL of blood in a pre-prepared anticoagulation tube (20 μL of peptidase, 20 μL of 10% EDTA-Na2); after being centrifuged, the plasma is collected for testing.

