### Analysis of the selection of PMOP-related scales

3.3

PMOP is often called the “silent killer” due to its high incidence and elusive nature, making it difficult for patients to detect and make decisions promptly. Therefore, clinical assessment through a reliable and efficient scale is crucial. The SF-MPQ scale is a reliable, objective, and sensitive evaluation method that can score patients’ pain characteristics, sensory features, emotional factors, etc., especially for assessing osteoporotic pain (67, 68). The scale includes emotional assessment items, such as weakness. Research has shown that OP and mental illnesses have similar biological pathways and common risk factors, such as old age, lack of physical activity, weight loss, and cognitive decline (69, 70). The symptom score of OP has a grading quantification feature, which is more detailed and scientific than other scales, and can evaluate OP-related symptoms from multiple dimensions.

Mental illnesses such as depression and anxiety are closely related to PMOP and need to be studied (71). There is a bidirectional regulatory relationship between OP and depression. On the one hand, OP causes physical pain and discomfort, leading to depression (72). On the other hand, depression accelerates the progression of OP (73). Emotional disorders such as depression and anxiety are closely related to bone metabolism. Studies have shown that chronic stress-induced emotional abnormalities cause bone loss through central nervous systems such as GABAergic neural circuits, sympathetic nervous systems, and glutamatergic neurons (74). CEA may also relieve emotional disorders such as anxiety and somatic anxiety by correcting the balance of excitatory and inhibitory amino acid neurotransmitters, which can affect the bone metabolism and play a role in treating PMOP (75). Depression is a risk factor for decreased BMD and can affect bone absorption and reconstruction processes by stimulating the sympathetic nervous system (SNS), leading to bone loss and OP. As an endocrine organ, bone can secrete bone factors that act on the hypothalamus, inducing depressive symptoms (76). The risk of cognitive impairment increases in postmenopausal women with OP (77, 78). Positive intervention can prevent or delay the occurrence of cognitive impairment in high-risk individuals. Consequently, We use the BDI-II and the MMSE to assess the psychological status and cognitive function in PMOP patients (79–82).

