Studies have shown that intervention with rTMS in DLPFC results in a corresponding change in leptin levels and that TMS may suppress food impulsivity in bulimic patients by modulating leptin levels (94). TMS has been found to modulate the neuroendocrine system, particularly leptin, by enhancing the PFC’s inhibitory capacity, which in turn effectively reduces BMI and impulsivity (94). Electroacupuncture altered the strength of resting functional connectivity in two brain regions, dorsal caudate and precuneus, in obese patients. This change negatively correlated with lower leptin levels and body mass index (95). Studies have shown that CEA can achieve weight loss by modulating leptin levels in the hypothalamus and solitary tract nucleus and the MAPK pathway in the prefrontal cortex of obese mice (96). Therefore, we speculate that stimulation of the DLPFC by low-frequency rTMS combined with CEA therapy reduces leptin secretion, inhibits sympathetic activity, and reduces norepinephrine secretion, thereby regulating bone metabolism.

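### The aim of elucidating a central mechanism has no brain measurement behind it, and a change in peripheral leptin cannot stand in for one

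*Protocol article*

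**What the plan says.** The Background of the abstract gives the trial two purposes: to study the effect of the combined treatment, and "to elucidate the central mechanism of this neural stimulation in regulating bone metabolism". The Introduction closes on the same purpose, to "elucidate the central mechanism of CEA combined with rTMS in regulating bone metabolism". There it follows a phrase about a preliminary look at correlations; the abstract carries no such qualifier.

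Section 2.11.2 sets out the biological readouts: "The leptin, leptin receptor, and norepinephrine levels of peripheral blood must be measured before and after treatment". Table 1 places them at weeks 0 and 12.

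Three other items come near the brain:

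- **Imaging.** The Introduction presents it as the origin of the hypothesis: "Based on the methods of the functional magnetic resonance imaging (fMRI) technique, we speculated". Section 3.2 also treats it as earlier work. It is not in Table 1 or in sections 2.10 and 2.11.
- **Electrophysiology.** Section 2.9.3 says: "The motor-evoked potentials (MEPs) are to be recorded in the contralateral" hand. The purpose is to set the motor threshold and the coil site at the first rTMS session.
- **Questionnaires.** Section 3.3 says: "We use the BDI-II and the MMSE to assess the psychological status and cognitive function in PMOP patients".

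On leptin and weight, section 3.4 cites work in which TMS modulated leptin, "which in turn effectively reduces BMI and impulsivity", and work in which "CEA can achieve weight loss by modulating leptin levels". The first sits in a passage on bulimia; the second was in obese mice. Weight is recorded at weeks 0 and 12 in Table 1.

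**The concern.** An aim to elucidate a central mechanism promises evidence about what happens between stimulation and bone. If every mechanistic observation is made in peripheral blood, the trial can show that a marker moved, and perhaps that it moved together with BMD or symptoms. It cannot show by what route.

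What is at stake is the conclusion that will be drawn. The Discussion part of the abstract already says, as fact, that each treatment regulates bone mass through its own central or peripheral route. With the aim as it stands, a fall in leptin, or a correlation between leptin and BMD, is likely to be reported as confirming that account. The design does not separate it from other explanations, and the protocol's own background supplies one of them by tying leptin to body weight.

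**Working it through.** There is no stated figure to reproduce. The check sets the aim beside the measurements and the analysis.

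**Step 1. Count what is measured.** The efficacy indicators in Table 1 are BMD and total efficiency of Chinese Medicine Symptoms (2), SF-MPQ and OSS (2), leptin, leptin receptor and norepinephrine (3), and MMSE and BDI-II (2): 2 + 2 + 3 + 2 = 9. Direct measures of brain structure or function: 0 of 9. Biological mechanism markers: 3 of 9, all from peripheral blood, at two time points.

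**Step 2. Check the near misses.** Imaging is prior work only. Motor-evoked potentials set the rTMS dose and site, are not listed as an outcome, and are not described for the CEA-alone arm. MMSE and BDI-II run at six time points, but they score cognition and mood; a change in either does not show that a brain-bone circuit was altered.

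**Step 3. Lay the hypothesised chain beside the data.** Section 3.4 proposes: stimulation of the DLPFC plus CEA, then less leptin secretion, then less sympathetic activity, then less norepinephrine, then an effect on bone. Leptin, norepinephrine and BMD are observed. The cortical or hypothalamic response and sympathetic activity itself are not. The links that would make the mechanism central are therefore the unobserved ones.

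**Step 4. Ask what each planned analysis could show.**

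- *Within-group before/after tests (section 2.14).* All three arms are active and no sham or untreated arm is described in section 2.1, so a within-arm fall in leptin has no reference against which to call it a treatment effect, central or otherwise.
- *Two-group tests.* Combined against CEA alone is a randomised contrast for adding rTMS, and combined against rTMS alone for adding CEA. A difference in leptin would be an effect on a peripheral marker. It does not say by which route.
- *Simple Pearson or Spearman correlations.* These are not randomised contrasts. They show association only.

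**Step 5. Weight.** Section 3.4 links leptin to BMI or weight for TMS, for electroacupuncture in obese patients and for CEA in obese mice. Section 3.3 lists weight loss among the risk factors that osteoporosis shares with mental illness. The document thus connects weight to the marker and to bone. Weight is recorded at the same two visits as the markers, and section 2.14 names no analysis that uses it. That is enough to leave a weight-related reading of a leptin change open. It is not enough to say how large, or in which direction, the influence would be.

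**The case against.** The strongest reply is that this is a matter of wording. The Introduction speaks of a preliminary investigation of correlations, section 3.4 says the pathway is speculation, and the contrast of combined treatment with CEA alone does randomise the addition of cortical stimulation, so it carries some indirect information on a central contribution. MMSE and BDI-II are indirect measures of brain function. All of this is fair, and it is why the remedy is a narrower aim. It does not rescue the aim as stated: the abstract is unqualified, and indirect information on whether adding rTMS matters is not a mechanism.

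A second reply is that covariates for secondary biomarkers are commonly left to the SAP, which is not shown. That stands. The absence of a weight adjustment is not the defect; the mismatch between aim and measurement is, and it holds whatever the SAP says.

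A reader might infer more from section 3.4 than it supports:

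- *That the protocol expects both treatments to cause weight loss in these patients.* It does not say so. The cited evidence concerns bulimia and obese mice.
- *That weight confounds the between-arm comparison of leptin.* It does not. Weight change comes after randomisation, and section 3.4 places leptin upstream of weight. For that comparison it is at most a mediator or a consequence.
- *That weight would imitate the hypothesised result.* If weight loss lowered both leptin and BMD, it would work against the hypothesised pattern of lower leptin with better bone. The issue is ambiguity, not a known bias.
- *That a size can be put on a weight-driven leptin difference.* The documents give neither a weight-change figure nor a leptin-weight correlation, so none can be derived.

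Section 2.14 also names no specific leptin-BMD correlation. That one will be run is a reasonable inference from the stated aims, not something the text fixes.

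**Conclusion.** The point holds for the aim. As described, the trial cannot elucidate a central mechanism at any sample size, because none of its nine efficacy indicators observes the brain directly and its three mechanism markers are peripheral. It can describe changes in those markers and their associations with BMD and symptoms. A change in leptin should not be reported as central action, and a weight-related explanation cannot be set aside on the protocol's own text.

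The conclusion rests on Table 1 and sections 2.10 and 2.11 being the complete outcome list, which is how they are presented. It does not bear on the primary outcomes, their type I error or their power. It changes what the trial may claim about mechanism.

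**What to change.** 1. In the abstract and at the end of the Introduction, restate the aim as exploratory: to describe changes in peripheral leptin, leptin receptor and norepinephrine, and their association with BMD and symptoms. State that no conclusion about a central mechanism will be drawn.
2. Compare the three markers between arms with adjustment for the marker's baseline value and for baseline weight.
3. If wanted, show marker-BMD correlations that also control for weight change from week 0 to week 12, labelled as supplementary description. They should not replace the planned correlations: weight change arises after randomisation and may be a consequence of leptin, so conditioning on it could remove part of the pathway of interest.

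The cost is a few sentences and a few lines of analysis. Baseline markers and weight at both visits are already scheduled, so no visit or sample is added. The price is a more modest stated aim. Section 2.16 says recruitment is under way, so the change should be dated and made before any marker results are seen.

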**Method:**

This trial is a prospective and randomized controlled trial. 96 PMOP participants will be randomized in a 1:1:1 ratio into a CEA group, an rTMS group, or a combined one. Participants will receive CEA, rTMS, or combined therapy for 3 months with 8 weeks of follow-up. The primary outcomes will be the changes in Bone Mineral Density scores, total efficiency of Chinese Medicine Symptoms before and after treatment. Secondary outcomes include the McGill Pain Questionnaire Short-Form, Osteoporosis Symptom Score, Mini-Mental State Examination, and Beck Depression Inventory-II. The leptin, leptin receptor, and norepinephrine levels of peripheral blood must be measured before and after treatment. Adverse events that occur during the trial will be recorded.

**Discussion:**

CEA achieves brain-bone mass regulation through the bottom-up way of peripheral-central while rTMS achieves it through the top-down stimulation of central-peripheral. CEA combined with rTMS can stimulate the peripheral-central at the same time and promote peripheral bone mass formation. The combination of CEA and rTMS may play a coordinating, synergistic, and side-effect-reducing role, which is of great clinical significance in exploring better treatment options for PMOP.

**Clinical trial registration**: https://www.chictr.org.cn/, identifier ChiCTR2300073863.

## Introduction

1

Postmenopausal osteoporosis (PMOP) is a systemic metabolic disorder characterized by reduced bone mass, degenerative alterations in bone tissue microstructure, and an elevated risk of bone fragility and fractures. This condition occurs in women after menopause due to ovarian dysfunction and decreased estrogen levels (1). This disease is characterized by back pain, kyphosis, height loss, spinal deformities, and pathological fractures. Osteoporotic fractures significantly contribute to increased morbidity and mortality in postmenopausal women (2). Women have a higher incidence of fractures than men, with a fracture rate twice that of men starting at age 50. Low bone mass is a significant risk factor for fractures in postmenopausal women (3). PMOP is currently a public health problem faced by the world, which not only significantly impacts the physical health and quality of life of patients but also brings a significant economic burden to the healthcare system (4). The direct medical costs of OP in the United States were estimated to be between 13.7 and 20.3 billion dollars in 2005. The price will reach 25.3 billion dollars by 2025 (5, 6).

The clinical treatment methods for PMOP mainly include medication and non-medication (7–9). Bisphosphonates are still the first-line medicine for OP, but potential long-term adverse reactions must be considered (10). A survey found that 19% of postmenopausal women diagnosed with OP did not receive anti-OP drug treatment, and 52% of patients refused the physician’s recommendation for drug treatment, mainly due to concerns about the potential side effects (11). Possible adverse reactions and patient resistance severely limit the clinical prevention and treatment of PMOP. Catgut embedding in acupoints (CEA) combines traditional acupuncture with modern medical theory. Guided by the idea of ‘deep and long-lasting insertion to treat chronic and stubborn diseases’, absorbable surgical sutures were creatively embedded deeply into acupoints during CEA to achieve sustained stimulation. Many clinical practices and studies have confirmed that CEA for PMOP has the advantages of good efficacy, safety, and reliability (12). The CEA has apparent advantages in overcoming and solving expensive medical costs, drug toxicity, and side effects, shortening traditional acupuncture treatment time, and improving patient compliance, which is worth further research (13). However, high-quality evidence from large-scale multicenter clinical randomized trials is still needed to support the treatment outcomes.

The nervous system also plays a regulatory role in bone remodeling and maintenance of bone mass. Scholars have found many neurotransmitters and hormones related to bone remodeling in the brain or brain-related organs and proposed mechanisms for crosstalk of the brain and bone (14–16). The theory of brain-bone mass regulation is of great significance for studying bone metabolism mechanisms. The brain regulates bone mass through neural-bone formation, neural-endocrine, and neuropeptide-bone regulation networks (17). Based on the methods of the functional magnetic resonance imaging (fMRI) technique, we speculated that the brain function and structure may play a crucial role in bone metabolism with PMOP. The CEA may exert its therapeutic effect on PMOP through the functional connection of the hypothalamic nuclei with the frontal cortex (18). CEA is a peripheral stimulation that regulates bone metabolism through the bottom-up, peripheral-central-peripheral pathway.

Repetitive transcranial magnetic stimulation (rTMS) generates a robust and rapidly changing magnetic field that induces current in the target area under the coil, thus activating cortical and subcortical neurons. It regulates neuronal excitability or inhibition, evaluates the corticospinal tract, and enhances brain plasticity (19, 20). This technique has been applied to evaluate the motor system, explore brain function, and investigate the pathophysiology of psychiatric disorders (21, 22). rTMS is currently an essential neuromodulation technique that can be used directly by stimulating the central targets in order to treat neurological diseases and peripheral systemic conditions (23, 24). Based on the neuro-bone mass regulation theory, we propose a central stimulation intervention to regulate bone metabolism by using the neuromodulatory effect of rTMS. We hypothesize that the combination of CEA and rTMS may have a coordinated, synergistic, and reaction-reduced effect, which has significant clinical value in exploring better treatment options for PMOP. The prevention and treatment of PMOP should not rely solely on peripheral interventions but also focus on central involvement. It is essential to integrate central and peripheral regulation for bone remodeling with the participation of the central and peripheral nervous systems.

CEA achieves brain bone mass regulation through the bottom-up peripheral-central way, while rTMS achieves it through the top-down stimulation of the central-peripheral (25). The combination of CEA and rTMS may achieve a bidirectional central-peripheral intervention on bone metabolism (26). Consequently, the study aims to explore the clinical effectiveness and safety of rTMS combined with CEA in treating PMOP from the perspective of central-peripheral regulation. We would like to preliminarily investigate the intrinsic correlation between CEA combined with rTMS, brain bone mass regulation, and clinical signs and elucidate the central mechanism of CEA combined with rTMS in regulating bone metabolism.

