### Design and study setting

2.1

A total of 96 participants meeting the diagnostic criteria for PMOP according to the guidelines of the clinical trial committee will be recruited at Bao’an Hospital of Traditional Chinese Medicine. Subjects will be informed of every study detail and sign an informed consent form.

This randomized, controlled clinical trial comprises three parallel groups. It compares the effectiveness of the individualized CEA group, CEA combined with the rTMS group and rTMS groups (Figure 1).

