### Interventions

2.9

Treatment strategies will be developed by consensus with experienced acupuncture practitioners and a neurologist. The trial is to include three groups: the CEA group, the combined group, and the rTMS group. The basic supplement regimen is as follows: 1000-1200 mg of calcium per day is recommended, which can be achieved through dietary intake or supplements. It is important to note that dietary calcium intake is recommended, but if dietary intake is insufficient, supplements can be used to compensate. Vitamin D intake of 800–1,000 international units (IU) per day is also recommended (29).

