#### The CEA combined with rTMS group

2.9.4

Subjects in this group will receive both the CEA and the rTMS treatment according to the respective regimens of the two therapies.

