### Statistical analysis

2.14

The data will be recorded and checked for accuracy, and the data related to baseline and clinical symptoms will be statistically analyzed using SPSS 27.0 software. The *t*-test will be performed for customarily distributed measures that meet the chi-squared test, and the *t′*test will be conducted for standards that meet the normal distribution but do not meet the chi-squared test. Independent sample *t*-tests are used between two groups, and paired sample *t*-tests will be used for pre-treatment and post-treatment comparisons within groups. Non-normally distributed measures are described by “median (interquartile range)” [*M (IQR)*], and non-parametric tests will be performed. *The Mann–Whitney U* test will compare two independent samples, and the *Wilcoxon Z* test will be used for pre-and post-treatment-comparisons. The scale scores at more than three of these time points are compared using repeated measures *ANOVA*. Correlations will be expressed as correlation coefficients (*r*). Correlations between the two measurement variables will be analyzed by Pearson correlation analysis if they conform to a normal distribution and Spearman analysis if they do not obey a normal distribution. Given that our study defines two primary outcomes, a Bonferroni correction will be applied, thus adjusting the significance level for individual outcome analyzes to *α*/2 to control the overall type I error rate, setting *α* = 0.05 (39).

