Clinical studies have demonstrated that acupuncture with TMS therapy is more effective than monotherapy in improving clinical symptoms (47, 48). Acupuncture activates various brain regions through a bottom-up modulation approach, while TMS generates action potentials in cortical axons that spread to other neurons via synapses, resulting in neuronal activation that spreads excitation to neighboring cortical and subcortical regions (49). The combination of these two treatments creates a pattern of central-peripheral and closed-loop stimulation that is superior for improving neurophysiological function (50, 51). CEA combined with rTMS can stimulate the peripheral-central simultaneously, thus correcting the imbalance of brain bone mass regulation and promoting peripheral bone mass formation (52–54). The combination of CEA and rTMS may play a coordinating, synergistic, and side-effect-reducing role (55), which is of great clinical value in exploring better treatment options for PMOP.

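### Synergy is hypothesised, but three active arms cannot estimate it, and before-after tests within arms cannot show that any arm works

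*Protocol article*

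**What the plan says.** The hypothesis is in the Introduction: "We hypothesize that the combination of CEA and rTMS may have a coordinated, synergistic, and reaction-reduced effect". The Discussion repeats the idea in section 3.1: "The combination of CEA and rTMS may play a coordinating, synergistic, and side-effect-reducing role". The abstract says much the same.

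The design is in the abstract and section 2.1. "96 PMOP participants will be randomized in a 1:1:1 ratio into a CEA group, an rTMS group, or a combined one". Section 2.1 adds: "It compares the effectiveness of the individualized CEA group, CEA combined with the rTMS group and rTMS groups". There is no sham, supplement-only or untreated arm. Section 2.9.4 describes the combined arm: "Subjects in this group will receive both the CEA and the rTMS treatment according to the respective regimens of the two therapies".

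Section 2.9 sets out a basic calcium and vitamin D regimen ahead of the three group regimens ("1000-1200 mg of calcium per day is recommended").

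Section 2.14 plans independent-sample tests between two groups, repeated-measures ANOVA for scales measured over time, and a Bonferroni correction across the two primary outcomes. It also plans paired tests that "will be used for pre-treatment and post-treatment comparisons within groups".

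**The concern.** A claim of synergy says that two treatments together do more than their separate effects add up to. To judge that, one must know what happens to patients who get neither. The design has no such patients, so its stated hypothesis and its arms do not match. A modest advantage of the combination over one single therapy could then be read as synergy.

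The paired tests raise a related problem. With large average changes from baseline, all three arms can show significant before-after differences without any of the treatments having caused them. If those tests were taken as evidence of effectiveness, the trial would appear to establish three effective treatments when it has no control against which to establish one.

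**Working it through.** **Inputs.** Section 2.8 gives pilot falls in the SF-MPQ PRI total: CEA 17.23 ± 2.84, rTMS 16.41 ± 1.77, combined 17.40 ± 2.17. I take the ± values as SDs of the change. Section 2.11.1.1 gives 15 descriptors scored 0 to 3, so the maximum is 45. The protocol offers no figure for synergy, so there is none to reproduce. The text lists SF-MPQ as secondary, but it is the only outcome with pilot values.

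**Additive synergy.** Let μ0 be the mean fall with neither treatment.

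I = combined - CEA - rTMS + μ0 = 17.40 - 17.23 - 16.41 + μ0 = μ0 - 16.24

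The protocol gives no μ0. Over an assumed range:

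| μ0 (assumed) | I |
|---|---|
| 0 | -16.24 |
| 5 | -11.24 |
| 10 | -6.24 |
| 15 | -1.24 |
| 17 | +0.76 |

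The sign depends wholly on the missing arm. A ratio scale does not help: for the effective rate, the multiplicative contrast (combined × neither) / (CEA × rTMS) needs the same missing cell.

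**Within-arm tests.** Mean change divided by SD is 17.23/2.84 = 6.1, 16.41/1.77 = 9.3 and 17.40/2.17 = 8.0. At 32 per arm, the paired t is that ratio times √32: about 34, 52 and 45. All three would be significant whatever the cause. Much smaller changes would be too. With a common SD of √((2.84² + 1.77² + 2.17²)/3) = 2.30 and 29 completers per arm (87/3), the standard error is 2.30/√29 = 0.43. A purely non-specific change of 2 points would then be significant with probability above 99%.

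**What the design can estimate about the combination.** (Normal approximation, 29 per arm, rejection in favour of the combination.)

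- Combined minus CEA: 17.40 - 17.23 = 0.17. SD = √((2.17² + 2.84²)/2) = 2.53, so d = 0.07. Power is about 4% at 0.05 and 2% at α/2 = 0.025. About 3,470 per arm would give 80% at 0.05.
- Combined minus rTMS: 17.40 - 16.41 = 0.99. SD = √((2.17² + 1.77²)/2) = 1.98. Power is about 48% at 0.05 and 37% at 0.025.

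**Error control.** The correction in section 2.14 covers two outcomes. Three arms give three pairs. If a significant result in any pair counted, the upper bound on the error rate would be 3 × 0.025 = 0.075 per outcome and 0.15 over both, counting BMD as one outcome. If success requires both contrasts of the combination, the false-success rate is at most 0.025 per outcome and 0.05 over both, with no further split.

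**The case against.** The wording is hedged, the stated aim is to explore effectiveness and safety, and no outcome or test is defined as synergy. The word could loosely mean better together. That is fair, but a hedged hypothesis still needs a design that can address it, and better than either alone is exactly what the restated hypothesis would say. An analysis plan that is not shown could name contrasts or mark tests as descriptive, but it could not add an arm.

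Several stronger readings are tempting, and the document does not support them.

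- *Side-effect reduction is untestable.* It is testable. Adverse events are recorded in all three randomised arms, so rates can be compared between the combined arm and each single arm. Receiving both regimens may make a reduction less plausible, but does not make it inestimable.
- *The design answers only one causal question.* CEA versus rTMS is also a randomised comparison.
- *The protocol uses paired tests as proof of efficacy.* Section 2.14 lists them without giving them that role, and it plans between-group tests as well.
- *The supplements are given to everyone.* Section 2.9 recommends an intake, and the calcium may come from diet.
- *The pilot shows sub-additivity.* It cannot. μ0 is unknown, and the scale is bounded at 45. With μ0 = 0, additivity would require a combined fall of 17.23 + 16.41 = 33.64 points. Baseline scores are not given, and patients may not have had that far to fall.

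**Conclusion.** The point holds for synergy and for the before-after tests. With CEA, rTMS and both as the only arms, the synergy contrast is not identified at any sample size. On the pilot figures it equals μ0 - 16.24, and the data will not determine its sign. The paired tests cannot support a claim that any arm works. The randomised comparisons between arms remain valid, so the fault lies in what the trial says it will show.

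The missing-arm argument rests on the design alone and needs no pilot value. The illustration assumes that the ± values are SDs, and the power figures also assume that the pilot differences are the true ones. They concern SF-MPQ and say nothing direct about power for BMD or the effective rate.

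**What to change.** 1. Restate the hypothesis: the combination is superior to CEA alone and to rTMS alone.
2. For each primary outcome, name combined versus CEA and combined versus rTMS as the confirmatory contrasts. Test each at the α/2 already assigned, and claim success for the combination only if both are significant.
3. Label the paired tests within arms descriptive.
4. State that the trial will not conclude synergy. The idea may stay in the rationale.
5. Keep side-effect reduction if wanted, but conclude it only from adverse event rates compared between the combined arm and each single arm.

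The cost is wording and analysis text. Recruitment has begun, so the change should be dated and made before outcome data are seen by group. The downside is a narrower claim and a demanding success rule, with very low power against CEA if the true difference is as small as the pilot SF-MPQ difference.

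A control cell would make synergy estimable, but not cheaply. With 96 patients in four cells of 24, the standard error of the interaction on SF-MPQ would be 2.30 × √(4/24) = 0.94, a 95% half-width of 1.84 points. An interaction of 0.99 points (assumed, equal to the pilot gap between combined and rTMS) would need about 170 per cell for 80% power.
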